## Abstract

**Background:**

Adolescent girls and young women (AGYW) in sub-Saharan Africa face a disproportionately higher HIV/AIDS burden despite the global decline in incidence. Existing interventions often fail to adequately address their unique social, economic, and cultural challenges, limiting access to essential HIV/AIDS services, including HIV testing. Emerging evidence indicates that HIV self-testing, a user-friendly and confidential method, enhances HIV diagnosis and linkage to care by targeting these barriers. This study aims to assess the feasibility, acceptability, and preliminary impact of a peer-delivered, community-health worker (CHW)-facilitated HIV self-testing intervention for AGYW in Northern Uganda.

**Methods:**

This mixed-methods quasi-experimental implementation science study will employ a three-fold approach. Firstly, we will conduct baseline formative qualitative research with 50 AGYW, 50 parents/partners to AGYW, 30 CHWs, 15 community leaders, and the district health office to inform the design of a peer-delivered CHW-facilitated HIV self-testing intervention tailored to AGYW’s needs in Northern Uganda. Secondly, we will implement a mixed-methods pilot study to assess the intervention’s feasibility and acceptability, involving 415 AGYW, 30 AGYW peer leaders, and 10 CHWs in selected parishes and villages in Omoro district, Northern Uganda. Lastly, we will evaluate the implementation outcomes and preliminary impact of the intervention on HIV self-testing rates and linkage to care by collecting and analyzing quantitative data pre- and post-intervention, laying the groundwork for a future robust randomized controlled trial.

**Discussion:**

Our intervention combines CHWs and peer-led strategies to address the unique challenges of AGYW in Northern Uganda, leveraging community resilience and peer influence. Successful completion of this project will provide a scalable model to be evaluated in a randomized trial and replicated in similar contexts.

**Trial registration number:**

PACTR202404851907736. Registered with the Pan-African Clinical Trials Registry on April 22, 2024.

**Supplementary Information:**

The online version contains supplementary material available at 10.1186/s43058-024-00596-7.

Contributions to the literature
Despite a global decline in HIV/AIDS incidence, adolescent girls and young women in sub-Saharan Africa still experience a disproportionately high burden of the disease.Urgent implementation science research is required to find solutions that enhance access to crucial HIV services for this at-risk population.This study aims to develop and assess a community-led HIV self-testing approach for adolescent girls and young women in Northern Uganda, leveraging peer leaders and community health workers.Our research seeks to establish the foundation for future robust trials investigating the impact of integrated community-based models on the uptake of HIV services in young people, both locally and internationally.

## Introduction

While there has been significant progress in combatting HIV/AIDS over the past three decades, adolescent girls and young women (AGYW), particularly in sub-Saharan Africa (SSA), remain disproportionately affected, emerging as a high-priority population [1, 2]. In 2022, there were 350,000 new cases of HIV among young people globally, and 60% of these were in AGYW [2]. Every week, of the 4,000 new cases of HIV/AIDS among AGYW worldwide, 77% were in SSA, and they accounted for nearly 63% of all new HIV diagnoses in young people in SSA [2]. In Uganda, of the 19,000 new HIV infections in young people aged 15–24 years, 79% were in AGYW, with the prevalence being almost four times higher than in males [2]. This disparity is majorly attributed to socioeconomic and cultural factors such as gender inequalities, limited education and employment opportunities for girls, and widespread gender-based violence, increasing their vulnerability to HIV [1, 3]. Child, early, and forced marriages, mainly due to poverty, limited access to adolescent-friendly sexual and reproductive health services, fear of stigma and discrimination, and unfair policies and laws in some countries, further contribute to the heightened risk [1, 3, 4].

HIV testing services (HTS) are an essential entry point to the HIV care cascade. By facilitating the diagnosis of HIV and early initiation of antiretroviral therapy (ART), HTS contributes to achieving viral suppression, improving clinical outcomes, and significantly reducing the risk of transmission [2]. Awareness of HIV status can empower individuals to make informed choices about their sexual health, including preventive measures. HTS are also routinely used to track the progression of the HIV epidemic, offering insights into the epidemic projections and the effectiveness of prevention strategies [2]. However, despite the importance of HTS, only 35% of 15–24-year-olds in SSA have ever been tested for HIV [5]. Additionally, only 66% of AGYW living with HIV in SSA are aware of their status, with an estimated 563,000 undiagnosed [5]. In Uganda, HIV testing rates among AGYW range between 43.4% and 84.4% [6–8]. Therefore, conventional health facilities and outreach HTS may not effectively reach all AGYW, especially those at the greatest risk. Barriers such as costs related to accessing HTS, the stigma associated with seeking such services, deeply rooted cultural and religious beliefs, and laws or policies requiring parental consent for HTS often hinder access [7, 9–11], especially in rural settings. Consequently, there is an urgent need for innovative, people-centered solutions to address these barriers [2, 12].

HIV self-testing (HIVST) has emerged over the past decade as an essential intervention to mitigate the challenges of conventional HTS. HIVST offers two modalities, blood-based and oral-fluid-based tests, with high sensitivity and specificity [13]. It has also been shown to be effective in diagnosing HIV in trials and real-world settings [14, 15]. HIVST is more preferred, acceptable, and feasible among AGYW, including in SSA [16–18]. In a fishing community in central Uganda, 74.2% of AGYW had heard about oral HIVST, and all were willing to use the kit if made freely available [19], while 93% of AGYW at a Ugandan tertiary institution were ready to use HIVST kits [20]. Despite robust evidence of its efficacy and tangible success in real-world settings, its uptake remains low in many high-risk populations [16]. Barriers to the implementation of HIVST include low awareness among AGYW, limited accessibility, high costs, stigma, and indirect obstacles like intimate partner violence [16]. Moreover, while HIVST offers initial diagnosis, challenges persist in linking those who test positive to timely and appropriate care, potentially leaving gaps in the treatment and management continuum [14].

Strategies like integration with existing sexual and reproductive health services [21], school-based distributions [22, 23], digital initiatives [24], and community-based models [19, 25] are potential options for increasing HIVST uptake among AGYW [14, 16]. Peer-led models have demonstrated promising outcomes, evidenced by studies in Kenya [26], Zimbabwe [27], South Africa [17], and Nigeria [28]. In a Ugandan fishing community, peer leaders distributed 99.3% of HIVST kits to AGYW, and 98.2% used the kit [19, 29]. In Kampala, all the 30 AGYW surveyed in a PrEP clinic embraced peer-delivered HIVST, citing its convenience, travel cost savings, reduced clinic waiting times, and stigma-free environment [30]. While CHW-led models have shown promise in delivering HIVST kits among AGYW in places like Malawi [25, 31, 32] and Zimbabwe [33, 34], a significant research gap among AGYW exists in Uganda. A recent CHW-led HIVST strategy targeting men in Uganda enhanced HIV testing rates, disclosure, and ART initiation [35, 36].

Recently, there have been calls from UNAIDS and an increasing recognition in the scientific community to embrace community-led initiatives in the response to HIV [37, 38]. To our knowledge, there are no published studies in Uganda evaluating the community-led HIVST model for AGYW in post-war Northern Uganda despite its unique sociocultural context. Our study aims to develop and evaluate the acceptability, feasibility, and preliminary effect of a peer-delivered and CHW-facilitated HIVST model among AGYW in rural Northern Uganda.

## Conceptual framework

The formative research phase of our intervention will be guided by a combination of two models: the Capability, Opportunity, and Motivation (COM-B) model [39] and the Health Belief Model (HBM) [40], providing a multifaceted lens through which to explore and understand the complexities of HIV testing among AGYW in Northern Uganda. The COM-B Model postulates that behavior (B) is a product of the interaction between Capability (C), Opportunity (O), and Motivation (M). In the context of our formative research, the COM-B Model will enable us to determine the various components that influence AGYW’s HIV testing behaviors and how these might be targeted in our intervention (Fig. 1). The HBM posits that individuals are more likely to engage in health-promoting behavior like HIV testing if they perceive themselves to be susceptible to a health problem, believe it has serious consequences, believe taking a specific action would reduce their susceptibility to or severity of the health problem, and believe the benefits of taking the action outweigh the costs or risks. The HBM will guide the exploration of beliefs and perceptions related to HIV and HIV testing, including self-testing, thereby informing strategies to enhance perceived benefits and minimize perceived barriers in our intervention.

**Fig. 1 Fig1:**
[figure not shown]
An illustration of the facilitators and barriers to HIV testing among adolescent girls and young women using the COM-B and the Health-Belief Models

The updated Consolidated Framework for Implementation Research (CFIR) [41] will be used to facilitate a comprehensive understanding of the multifaceted factors influencing the implementation of CHW-facilitated peer-led HIVST intervention among AGYW in rural Northern Uganda (Fig. 2). The **innovation**, OraQuick, manufactured by OraSure Technologies, is a rapid HIV self-test that uses an oral swab to detect antibodies to HIV-1 and HIV-2. Its efficacy has been demonstrated in numerous trials and real-world settings, showcasing its potential as an effective tool for HIV screening. The sensitivity of OraQuick ranges from 97.7 − 99.6% and specificity from 96.8 − 99.9%, emphasizing its accuracy and reliability. The test was approved by the U.S. Food and Drug Administration (FDA) in 2012 and is listed among accepted pre-qualified in vitro diagnostics by the World Health Organization. Evidence suggests that it is simple to use by AGYW with minimal or no supervision and returns results within 20 min. In the Ugandan retail pharmacies, it costs between 7 USD – 10 USD.

In the **o****uter setting**, the sociocultural values of the local ethnic groups in this region and the economic circumstances will significantly influence the acceptability and feasibility of our intervention. Northern Uganda is mainly inhabited by two ethnic groups - Acholi and Lango - who belong to the Luo origin and dialect and share many similarities in language and culture. The Acholi and Lango occupy the Acholi and Lango sub-regions, respectively. In addition to social and cultural values, partnership with the local leaders and adherence to policies and laws while respecting local traditions will facilitate the smooth delivery of the intervention. Anticipated critical events include inconclusive results, emotional and psychological impact on individuals receiving positive results, confidentiality breaches, stigma, discrimination, and navigating ethical dilemmas related to disclosure, particularly in AGYW with guardians or partners. The implementation team shall undergo didactic training before and during the intervention to mitigate such events.

The **inner setting**, which includes the physical infrastructure (the nearby health facilities in each sub-country), work infrastructure (health workers, including CHWs), and the organization of the community, is essential to the success of the intervention. Ensuring that the intervention aligns with the norms and values of the CHWs and the community, and prioritizing communication with stakeholders, will be critical for effectively navigating the complex intervention environment. The target **individuals** in this study are AGYW, aged 15–24 years, in Omoro district, and they are the innovation recipients. The high-level leaders include the local government officials of Omoro district, particularly the district Chief Administrative Officer and the District Chairperson, whose approval will be sought before project implementation. The District Health Officer of the district and Lalogi Health Sub-District in charge are mid-level leaders and will provide technical support and guidance in mobilizing health workers needed for confirmatory testing, linkage to care, ART initiation, and follow-up. The village local council chairpersons, who are also mid-level leaders, will facilitate community entry and mobilization. The CHWs are the implementation facilitators, while the AGYW peer leaders are the innovation deliverers. The investigative team will be the implementation leads. The formative research will provide more insights into the characteristics of the individuals regarding their capability, opportunities, motivation, and needs.

Finally, the **implementation process**, as previously described, will involve formative research to assess the needs and context, adapting and tailoring strategies to the local context, and teaming up AGYW leaders with CHWs. This will, in turn, strengthen the already existing working relationships between CHWs and the nearest health facilities for effective linkage to care.

**Fig. 2 Fig2:**
[figure not shown]
The updated Consolidated Framework for Implementation Research showing factors that may influence the implementation of a peer-led CHW-facilitated HIVST among AGYW in Northern Uganda (Image adapted from The Center for Implementation [42])

The Social Cognitive Theory (SCT), an essential framework for understanding, predicting, and altering human behaviour, shall be used to describe the theory of change while evaluating the preliminary effects of the intervention [43]. The SCT postulates that human learning and behaviour are products of a dynamic interplay between personal, behavioral, and environmental factors. It emphasizes the role of observational learning, motivational processes, attention, retention, self-efficacy, and outcome expectations in behavior development and maintenance. In our context, AGYW are more likely to accept HIVST when promoted, distributed, trained, counselled, and facilitated by their peers who live within their communities who are relatable to them. Seeing or hearing feedback that other peers are also engaging in HIVST can reduce the fear and stigma associated with the testing process, promoting its adoption. Feedback from peers about the benefits of HIVST, like early detection, better outcomes, and peace of mind that comes with knowing their status, they may be more likely to accept HIVST and linkage to care. Furthermore, using AGYW-peer-leaders to distribute HIVST kits recognizes young people as important stakeholders in their own health, capturing the attention of fellow AGYW better, improving sustainability, and promoting community resilience.

## Methods and materials

### Aims

The overall aim of this study is to establish a sustainable, community-based HIV self-testing model that effectively increases HIV rates and linkage to care among AGYW in Northern Uganda. The specific aims are:To develop a peer-delivered CHW-facilitated HIV self-testing model tailored to the needs of AGYW in Northern Uganda.To evaluate the feasibility and acceptability of the peer-delivered CHW-facilitated HIVST intervention in Northern Uganda.To assess the preliminary impact of the peer-delivered CHW-facilitated HIVST model on HIV self-testing rates and linkage to care among AGYW.

### Study design

This will be a quasi-experimental mixed-methods implementation study utilizing both qualitative and quantitative methods. This protocol adheres to the Standard Protocol Items: Recommendations for Interventional Trials (SPIRIT) statement [44] and the Template for Intervention Description and Replication (TIDieR) guidance [45]. Filled copies of the checklists are attached as Supplementary File 2 and Supplementary File 3, respectively.

### Study setting

This study will be conducted in Omoro district, located south of Gulu and North of Kampala, Uganda’s capital city. Omoro is one of the districts affected most by over two decades of civil conflict in Northern Uganda, which led to mass destruction of property, displacement, and loss of lives. It is also among the poorest districts in the region and the country, with a GDP per capita of 183 USD [46]. Lalogi Health Center IV is the district’s largest public health facility, with 5 Health Center IIIs and 15 Health Center IIs. CHWs (also known as village health teams) provide the first line of healthcare at the village level, mainly preventive and referral services. Omoro is divided into Tochi and Omoro counties and has twelve sub-counties.

### Study population

The primary target population for this study is adolescent girls and young women (AGYW) aged 15–24 years living in Omoro district of Northern Uganda. The secondary target population are community health workers (village health team members) and the local council leaders in Omoro district.

### Sample size and sampling techniques

A multistage random sampling method will be employed to select study participants representative of the district’s population. Initially, we will randomly select five sub-counties from the available twelve in the district. One parish will then be selected randomly from each of the five sub-counties as study sites. For the baseline qualitative focus group discussions (FGDs), a total of 50 matched pairs of AGYW and their parents or spouses (for AGYW in marriage or union) will be selected using purposive sampling across five parishes. We will identify ten homesteads in each parish in collaboration with local council leaders, aiming to ensure a diverse representation of geographical, educational, and socioeconomic backgrounds. This number is based on evidence suggesting that saturation in qualitative studies often occurs by the twelfth interview, with minimal new information beyond 20–30 interviews [47]. A larger sample size was chosen to capture a diverse range of experiences and perspectives within this group from all the five selected parishes. Recognizing the iterative nature of the qualitative methods, we will also implement adaptive sampling strategies, allowing for the inclusion of additional participants or specific subgroups as new themes emerge until no new information is obtained and saturation is reached. Thirty CHWs and fifteen community leaders (local council chairpersons I, II, and IIIs) will be purposively selected, in line with qualitative research methodologies that recommend smaller, focused samples for specialized groups [48], to adequately explore their unique perspectives on the HIV self-testing model.

The sample size for the quantitative pre- and post-intervention quantitative survey among AGYW was calculated using Epi Info StatCalc for population surveys and was powered with acceptability as the primary outcome variable. As of the last national census, females make up 51% of the population in Omoro, leading to an estimated population of 16,383 AGYWs. At an average population growth rate of 3.2% between 2014 and 2022, the estimated population of AGYW in Omoro district is 21,753 by the end of 2023. To estimate the acceptability of HIVST among AGYW with an estimated population size of 21,753, expected acceptability of 50% since no previous studies have been conducted in this region, a margin of error of ± 5% at a 95% confidence level, and a design effect of 1.0, we determined that a sample size of at least 377 AGYW is required. To cater for non-response and loss-to-follow-up, an additional 10% of the sample size will be added, leading to a final sample size of 415 AGYW. The study participants will be selected through systematic random sampling, depending on the number of households obtained from the local council leaders. First, we will obtain the number of potentially eligible homesteads from the local council chairpersons in the selected parishes. We will then calculate the sampling interval (k) by dividing the total number of eligible homesteads by the desired sample size. Starting with a random point between 1 and k, we will select every kth person from the list for participation. In circumstances where the household members are not around during the interview or decline consent, we shall consider the next immediate household and then resume the sampling interval.

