### Data management and analysis

The FGDs and KIIs recordings will be transcribed verbatim, translated to English, and exported to *Atlas.ti* for thematic content analysis to inform the development and adaptation of intervention. Transcriptions from the FGDs and KIIs will be thematically analysed to identify themes related to implementation outcomes, experiences, barriers, and facilitators of peer-delivered CHW-facilitated HIVST. Upon importing the transcribed data into Atlas.ti, we will initially conduct a thorough reading to familiarize ourselves with the content, marking significant and recurrent themes related to barriers and facilitators to HIV and HIVST among AGYW in Northern Uganda. Coding will be performed iteratively, with initial codes generated from the data being grouped into broader themes and sub-themes that capture the nuances of participants’ experiences and perceptions.

Quantitative data from the semi-structured questionnaires and observational checklists will be collected by trained research assistants using RedCap™ deployed into a tablet, uploaded on secure cloud storage, and exported to STATA 18.0 and R Software for cleaning, coding, and analysis. At the univariate level, we will describe demographic characteristics and implementation outcomes using frequencies and percentages for categorical variables, means and standard deviation for normally distributed continuous variables, and median and interquartile range for non-parametric distribution. Factors associated with acceptability will be assessed using multilevel logistic regression models, adjusting for confounders. Factors to be included in the model will be selected from the literature review guided by the COM-B, HBM, and CFIR theoretical frameworks and expert opinion. We will also evaluate changes in the implementation outcomes before and after the intervention using paired t-test, Mann-Whiney U test, and McNemar’s Test, appropriately. A *p*-value < 0.05 will be considered statistically significant. We will estimate the overall cost of implementing the intervention using the data recorded in the financial books. The costs per HIV test kit distributed, HIV test performed, and HIV diagnosis will be calculated to facilitate a cost-benefit analysis of the model.

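### The ±5-point precision for acceptability rests on a design effect of 1.0, but the sample is clustered in five parishes and is meant to represent the district

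*Protocol article*

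**What the plan says.** All of this is in the Protocol article. Under Sample size and sampling techniques, the pre- and post-intervention survey "was powered with acceptability as the primary outcome variable". The inputs are "expected acceptability of 50% since no previous studies have been conducted in this region", a margin of ±5 points, and the whole district as the finite population: "the estimated population of AGYW in Omoro district is 21,753 by the end of 2023". The result is given "at a 95% confidence level, and a design effect of 1.0, we determined that a sample size of at least 377 AGYW is required". The only inflation is for non-response and loss to follow-up: "an additional 10% of the sample size will be added, leading to a final sample size of 415 AGYW".

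The same section sets out the sampling: "A multistage random sampling method will be employed to select study participants representative of the district’s population". Five of the twelve sub-counties are drawn at random, and "One parish will then be selected randomly from each of the five sub-counties as study sites". Under Baseline pre-intervention survey, all 415 AGYW come from those five parishes by systematic household sampling.

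Under Data management and analysis, implementation outcomes are described with frequencies and percentages. Pre-post changes are tested with the paired t-test, a rank test and McNemar's test. "Factors associated with acceptability will be assessed using multilevel logistic regression models, adjusting for confounders". No levels are named for that model, and no interval method is named for the percentages.

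**The concern.** The sample size treats the 377 AGYW as independent draws from the district's 21,753. The design first selects five places and then takes everyone from them. AGYW in one parish share a health facility, local leaders, peer leaders and social norms, all of which can move acceptability. If parishes differ at all, 377 AGYW from five of them say less about the district than 377 AGYW drawn across it. A design effect of 1.0 assumes an ICC of exactly zero, and the article gives no reason for that.

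Acceptability is the outcome on which the survey was sized, and the study is meant to prepare a randomised trial. At stake is whether a reader, or the planner of that trial, can take the district estimate as good to ±5 points.

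**Working it through.** **Inputs from the article:** p = 0.50; d = 0.05; 95% confidence (z = 1.960); N = 21,753; design effect 1.0; 5 parishes, one in each of 5 of 12 sub-counties; n = 377, raised to 415.

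**Assumed, not in the article:** parish ICC of 0.01, 0.02 or 0.05; equal numbers per parish, m = 377/5 = 75.4.

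**Step 1. Reproduce the plan's figure.**
- n0 = z²p(1−p)/d² = 384.1.
- With the finite population: n = 384.1/(1 + 383.1/21,753) = 377.5, which matches 377.
- Allowance: 377 × 1.10 = 414.7, which matches 415.

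The calculation is right for a design effect of 1.0. At 377 the margin is already 5.0 points, so nothing is left for clustering.

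**Step 2. Put in the clustering.** DEFF = 1 + (m − 1) × ICC = 1 + 74.4 × ICC. Margin = z × √(DEFF × 0.25/377) × √((21,753 − 377)/21,752). The last factor is 0.991.

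**Step 3. Credit the first-stage sampling fraction.** Taking 5 of 12 sub-counties reduces the between-parish part by 1 − 5/12 = 7/12: variance = 0.25 × [(ICC/5) × 7/12 + (1 − ICC)/377]. This is generous, because only one parish is taken in each sub-county, so the differences among parishes within a sub-county are not reduced by that fraction.

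**Step 4. Small number of parishes.** With five parishes the reference is t on 4 degrees of freedom, 2.776 instead of 1.960, which multiplies each margin by 1.417.

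| Assumed ICC | DEFF | Effective n | Margin, z (step 2) | Margin, z, 5-of-12 correction (step 3) | Step 2 with t, 4 df | Step 3 with t, 4 df |
|---|---|---|---|---|---|---|
| 0.01 | 1.74 | 216 | ±6.6 | ±6.0 | ±9.4 | ±8.5 |
| 0.02 | 2.49 | 152 | ±7.9 | ±6.9 | ±11.2 | ±9.8 |
| 0.05 | 4.72 | 80 | ±10.9 | ±9.0 | ±15.4 | ±12.7 |

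**Step 5. Can the 10% allowance cover it?** If nobody were lost, 415 would absorb a design effect of about 1.08 (415/384.1) to 1.10 (415/377). With 83 per parish that is an ICC of about 0.001. The allowance is already committed to non-response and loss.

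**Step 6. Would more AGYW in the same parishes help?** As n grows, the step 2 variance falls only to 0.25 × ICC/5. Setting this equal to (0.05/1.96)² gives ICC = 0.013. Above that value, no number of AGYW from five parishes reaches ±5 points. With the step 3 correction the limit is 0.013 × 12/7 = 0.022. The number of parishes is the binding constraint.

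**The case against.** **The ICC is unknown, so the shortfall could be small.** This stands for the size but not for the direction. Both variance formulas rise with the ICC from the first increment: per unit of ICC, the between-parish term adds 1/5 (or 7/60 with the 5-of-12 correction) and the within-parish term takes off only 1/377.

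**Five of twelve sub-counties is a large fraction.** This also stands in part. It brings the z-based range down to about ±6.0 to ±9.0 and belongs in any fair statement of the size. It does not restore ±5.

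**Acceptability may be well above 50%.** The Introduction cites high willingness among Ugandan AGYW. With p = 0.90 and n = 377, ±5 points survives a design effect up to (0.05/1.96)² × 377/0.09 = 2.7 (ICC about 0.023). With p = 0.93 the limit is 3.8 (ICC about 0.037). So the achieved margin could turn out near ±5 on the z basis. The plan chose 50% and does not rely on a higher value, so its stated precision has to be judged at 50%.

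**The five parishes could be treated as fixed.** A design effect near 1 could then be defended, but only for those parishes. That conflicts with the district claim and with the district population used in the formula.

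**Interval methods belong in the analysis plan.** Agreed. A reader might infer that an interval ignoring clustering will be computed and published as ±5. The article names no interval method, so this cannot be said. A reader might also infer from the multilevel model that the plan concedes clustering by parish. It names no levels, and these could be villages, peer leaders or repeated surveys of one person. It suggests awareness of clustering and no more. The point rests on the precision that the article itself states, which no later analysis can add back.

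**Conclusion.** The point holds as a mismatch between the stated precision and the stated design. It is not an arithmetic error: 377 and 415 are correct for their inputs, and the input that does not fit is the design effect of 1.0. At p = 50% with 377 analysed, ±5 points for the district is not delivered for any positive parish ICC.

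The size rests on an assumed ICC of 0.01 to 0.05 and equal parish sizes: about ±6.6 to ±10.9 points, or about ±6.0 to ±9.0 with the generous first-stage correction, and wider on 4 degrees of freedom. These margins are for a single-survey proportion. They do not carry over to the paired pre-post change, where stable parish differences partly cancel.

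A reader might infer that the sample must be enlarged. The documents do not support that. This is a pilot, no decision threshold in the article depends on ±5, and step 6 shows that more AGYW in the same parishes has limited value.

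**What to change.** Keep n = 415 and make three changes.

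1. **Precision statement.** Replace ±5 points at a design effect of 1.0 with the range above and the ICC that it assumes. For example: with 377 analysed in five parishes and acceptability of 50%, the expected 95% margin for the district is about ±6.6 to ±10.9 points for a parish ICC of 0.01 to 0.05 (about ±6.0 to ±9.0 with a correction for sampling five of twelve sub-counties), and wider with t on 4 degrees of freedom. The alternative is to limit the ±5 to the five selected parishes and drop the claim to represent the district.
2. **Analysis.** Compute district-level intervals for AGYW acceptability, and the pre-post comparison, allowing for clustering by parish with a small-sample reference on 4 degrees of freedom.
3. **ICC.** Report any parish ICC with its interval and the caveat that five parishes estimate it poorly, so that the future trial does not plan on the point estimate alone.

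The cost is wording in the sample size section and survey or cluster commands in software that the study already uses. The stated precision becomes less favourable. No extra participants are needed.
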